# TRansfusion strategies in Acute brain INjured patients (TRAIN): a prospective multicenter randomized interventional trial protocol

**DOI:** 10.1186/s13063-022-07061-7

**Published:** 2023-01-07

**Keywords:** Anemia, Brain perfusions, Tissue hypoxia, Brain injury, Outcome, Clinical study, Randomized controlled trial

## Abstract

**Background:**

Although blood transfusions can be lifesaving in severe hemorrhage, they can also have potential complications. As anemia has also been associated with poor outcomes in critically ill patients, determining an optimal transfusion trigger is a real challenge for clinicians. This is even more important in patients with acute brain injury who were not specifically evaluated in previous large randomized clinical trials. Neurological patients may be particularly sensitive to anemic brain hypoxia because of the exhausted cerebrovascular reserve, which adjusts cerebral blood flow to tissue oxygen demand.

**Methods:**

We described herein the methodology of a prospective, multicenter, randomized, pragmatic trial comparing two different strategies for red blood cell transfusion in patients with acute brain injury: a “liberal” strategy in which the aim is to maintain hemoglobin (Hb) concentrations greater than 9 g/dL and a “restrictive” approach in which the aim is to maintain Hb concentrations greater than 7 g/dL. The target population is patients suffering from traumatic brain injury (TBI), subarachnoid hemorrhage (SAH), or intracerebral hemorrhage (ICH). The primary outcome is the unfavorable neurological outcome, evaluated using the extended Glasgow Outcome Scale (eGOS) of 1–5 at 180 days after the initial injury. Secondary outcomes include, among others, 28-day survival, intensive care unit (ICU) and hospital lengths of stay, the occurrence of extra-cerebral organ dysfunction/failure, and the development of any infection or thromboembolic events. The estimated sample size is 794 patients to demonstrate a reduction in the primary outcome from 50 to 39% between groups (397 patients in each arm). The study was initiated in 2016 in several ICUs and will be completed in December 2022.

**Discussion:**

This trial will assess the impact of a liberal versus conservative strategy of blood transfusion in a large cohort of critically ill patients with a primary acute brain injury. The results of this trial will help to improve blood product and transfusion use in this specific patient population and will provide additional data in some subgroups of patients at high risk of brain ischemia, such as those with intracranial hypertension or cerebral vasospasm.

**Trial registration:**

ClinicalTrials.gov NCT02968654.

**Supplementary Information:**

The online version contains supplementary material available at 10.1186/s13063-022-07061-7.

## Administrative information

The numbers in brackets at each paragraph in this protocol refer to SPIRIT checklist item numbers. The order of the items has been modified to group similar items (see http://www.equator-network.org/reporting-guidelines/spirit-2013-statement-defining-standard-protocol-items-for-clinical-trials/). The SPIRIT Checklist has been submitted as Supplemental Material.

## Background and rationale

Although red blood cell transfusion (RBCT) can be lifesaving in extreme circumstances, in the absence of life-threatening hemorrhage, the indications for RBCT are somewhat controversial. Blood transfusions have well-recognized problems, including the need to type and cross-match, the potential transmission of diseases, and the development of transfusion-related complications (such as transfusion-related acute lung injury—TRALI—or transfusion-associated circulatory overload—TACO) and immunosuppression [1–3]. However, anemia has also been associated with increased morbidity and mortality among critically ill patients [4, 5]. As such, determining who and when to transfuse in this patient population is thus a challenge and recent years have seen continuing debate and discussion regarding the optimal transfusion “trigger” [6].

In a landmark multicenter Canadian trial, Hebert and colleagues [7] randomized 838 critically ill patients to either a liberal protocol in which transfusions were administered to maintain hemoglobin levels greater than 9 g/dL or a restrictive strategy in which hemoglobin levels were kept between 7 and 9 g/dL. Overall, the 30-day mortality rate was 19% in the restrictive group and 23% in the liberal transfusion group (i.e., non-significant difference), with a significant lower mortality among younger patients and less sick patients, when randomized to the restrictive strategy group. The ABC study [8], an epidemiological survey of 3534 patients conducted in 146 ICUs of West Europe, confirmed an increased mortality rate in transfused patients, even after adjustment for several confounders. In contrast, the analysis from the Sepsis Occurrence in Acutely Ill Patients (SOAP) database (*n* = 3147) found no significant association of RBCT with an increased risk of death after a multivariable analysis and propensity matching [9]. These results had a definite influence on ICU practice, encouraging intensivists to limit the use of transfusions. Moreover, more recent randomized trials have also suggested that a restrictive transfusion policy might be safe and as effective as a more liberal one in critically ill patients [6, 10].

Importantly, most of these studies did not consider the presence of acute brain injury as a specific target population in whom transfusion threshold could be critical. Several observational studies have shown that Hb levels less than 9 g/dL were associated with a poorer outcome in patients with traumatic brain injury (TBI) or subarachnoid hemorrhage (SAH) [11, 12]. On the other hand, the administration of red blood cells (RBC) was also associated with an increased risk of complications or mortality in this setting [13, 14]. A recent meta-analysis showed that studies aimed at comparing two different transfusion thresholds in these patient populations were largely underpowered to identify the best Hb levels [15]. Accordingly, the effects of transfusion need to be better assessed in acute brain injury. One recent randomized clinical trial compared, in a factorial design, the effects of erythropoietin and two Hb transfusion thresholds (7 g/dL vs. 10 g/dL) on neurological recovery after TBI (*n* = 200) [16]. There were no significant differences in the occurrence of favorable neurological outcomes between groups (43% for 7 g/dL and 33% for 10 g/dL, *p* = 0.28). Moreover, there was a higher incidence of thromboembolic events for the transfusion threshold of 10 g/dL (22% vs. 8%; *p* = 0.009). Nevertheless, the number of patients included in the study was relatively small and the two groups of patients showed mean Hb levels much higher than those associated with the treatment arm to which they were randomized.

### Interventions: description

Patients are randomized to two different thresholds of Hb to determine when RBC transfusion should be initiated (< 7 g/dL vs. < 9 g/dL). After randomization, all patients should preferably receive one unit of RBC at a time. Patients randomized to the lower Hb threshold for transfusion receive packed RBC transfusion whenever their Hb concentration is < 7 g/dL; similarly, patients randomized to the higher threshold are transfused whenever their Hb concentration is < 9 g/dL. Transfusion thresholds are maintained until a maximum of 28 days after randomization or hospital discharge/death, whichever occurs first. Daily Hb concentrations are recorded according to local practices; values from blood gas analyses are also allowed during the ICU stay to avoid protocol violation. Patients can be included in the study only once.

#### Interventions: modifications

Protocol violation is defined as one of the following: (a) inability to maintain the daily max Hb values < 9 g/dL in the restrictive group and avoid transfusion until Hb drops below 7 g/dL OR > 9 g/dL in the liberal group for two consecutive days, (b) one or more transfusions given inappropriately (i.e., in contradiction of the assigned trigger level), and (c) error in type/cross-match between donor and recipient.

Crossover to another treatment arm than allocated is allowed based on the decision of the treating physician, such as (1) acute coronary syndrome, requiring a higher Hb level; (2) acute bleeding requiring multiple RBCT; and (3) lack of available blood. The reason for crossover or protocol violation will be mentioned in the electronic case report form (eCRF).

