### Composition of the data safety monitoring committee, its role, and reporting structure

The study is considered as a low-risk study; a Data Monitoring Safety Committee (DMC) has been created to perform the interim analyses for safety, futility, or efficacy so that the executive and steering committee can remain blinded for the study outcomes. All the DMSC members (Supplemental Table 2) have no conflict of interest with the sponsor of the study and are not involved in the study. DMSC membership is for the duration of the clinical trial. The DMSC has therefore monitored inclusion rate, losses to follow-up, or potential harms, making the recommendation that the trial continues to recruit participants or whether recruitment should be terminated earlier.

**Table 2 Tab2:** Serious adverse event (SAE) of the TRAIN study

SAE	Definition
Severe hypertension	Mean arterial pressure (MAP) > 130 mmHg for more than 1 h and needing active therapy, in the absence of vasopressor agents and increased intracranial hypertension
Severe hypotension	MAP < 65 mmHg for at least > 1 h, not responding to fluid therapy and needing vasopressor therapy, in the absence of active bleeding
Venous thrombotic events	Deep vein thrombosis (formation of a blood clot within a deep vein in the legs or arms, which may be associated with non-specific signs, such as pain, swelling, redness, warmness, and engorged superficial veins—it can be diagnosed either by echography, venography, or CT imaging); pulmonary embolism (formation of a clot within the pulmonary arterial circulation, diagnosed by contrast pulmonary CT scan or echocardiography)
Acute myocardial ischemia	Acute myocardial infarction (ST-elevation and non-ST-elevation myocardial infarction) or unstable chest pain diagnosed during current hospital admission, according to specific criteria (i.e., elevated biomarkers of myocardial injury, ischemic signs on ECG, clinical suspicion) and the patient has received specific treatment (reperfusion strategies such as percutaneous coronary intervention [PCI] or thrombolysis) or initiation/increase of antithrombotic drug treatment during current ICU admission
Intestinal ischemia	Ischemic lesions confirmed by endoscopy and/or open surgery
Acute peripheral limb ischemia	Clinical signs and the need for open or percutaneous vascular intervention, amputation, or initiation/increased antithrombotic treatment

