### Informed consent

Written informed consent must be obtained prior to the randomization to the study. Because of the difficulties predicting the exact moment at which anemia may occur during the ICU stay, it is recommended that written informed consent be obtained as soon as possible after ICU admission so that randomization can be performed rapidly when the inclusion criteria are met. For patients who are unable to consent, their legal representatives are informed of the study as soon as possible and must sign for participation in the trial before randomization. Subjects with sufficient neurological recovery are informed of their study participation and be asked to provide their consent for the use of their data. Patients or next of kin can withdraw consent at any time during the study without giving a specific reason. Withdrawal should not influence the standard of care, with an Hb threshold for RBC transfusion that will then be decided by the attending physician. Patients withdrawing from the study are asked to consent for the inclusion of data collected before withdrawal. The site investigator may also withdraw a subject from the study for safety reasons (e.g., acute myocardial infarction needing higher Hb levels).

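### One coronary event can be a crossover or a study withdrawal, so keeping the 180-day eGOS may depend on the site; read literally, violation (b) also counts permitted crossovers

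*Protocol article*

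**What the plan says.** *Interventions: modifications* has two paragraphs on departures from the assigned threshold. The first defines protocol violations; limb (b) is "one or more transfusions given inappropriately (i.e., in contradiction of the assigned trigger level". The second leaves crossover to the treating physician, with examples: "such as (1) acute coronary syndrome, requiring a higher Hb level; (2) acute bleeding requiring multiple RBCT; and (3) lack of available blood". It closes with the recording rule: "The reason for crossover or protocol violation will be mentioned in the electronic case report form (eCRF".

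*Informed consent* adds another route: "The site investigator may also withdraw a subject from the study for safety reasons (e.g., acute myocardial infarction needing higher Hb levels". On data after withdrawal it says only: "Patients withdrawing from the study are asked to consent for the inclusion of data collected before withdrawal".

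Table 2 puts infarction and unstable chest pain under one serious adverse event: "Acute myocardial infarction (ST-elevation and non-ST-elevation myocardial infarction) or unstable chest pain diagnosed during current hospital admission".

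The primary analysis is by intention to treat (*Statistical methods: outcomes*). The section on non-adherence and missing data plans no per-protocol or as-treated analysis, expects very few crossovers or losses, and rules out imputation of missing outcomes. Protocol compliance was one of the items examined at the 300-patient interim (*Interim analysis*).

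**The concern.** Myocardial infarction is an acute coronary syndrome, and both sections attach the same condition, a need for a higher Hb. In one the patient crosses over and remains in the trial. In the other the patient can be taken out of it. Two sites can follow the text and give the same patient different statuses.

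The status matters because it may decide whether the primary outcome is observed. After a crossover the 180-day eGOS is collected and analysed as randomized. After a withdrawal its collection is not stated. A gap of that kind would follow a listed serious adverse event and depend on local choice, so it could not be assumed random.

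The second matter is smaller. If a transfusion under a permitted crossover also counts as violation (b), the compliance tables mix allowed care with error.

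**Working it through.** The point is textual and no stated figure depends on it, so the sections are compared first.

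**Coronary event needing a higher Hb**

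| | *Interventions: modifications* | *Informed consent* |
|---|---|---|
| Status | crossover | withdrawal from the study |
| Decided by | treating physician | site investigator |
| Force | permitted | permitted |
| 180-day eGOS | kept under intention to treat | collection afterwards not stated |
| If eGOS is missing | – | not imputed |

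**Violation (b).** The i.e. clause explains what counts as inappropriate by the trigger alone. A restrictive-arm patient transfused at Hb 8 g/dL under an allowed crossover has been transfused against the assigned trigger of below 7 g/dL, so (b) is met. The following paragraph permits the same transfusion. The recording rule names crossover and violation as alternatives but does not separate them.

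**Illustration of size.** The documents give no rate for coronary events or crossovers, so shares of 2%, 5% and 10% are assumed.

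Inputs from *Sample size*: 50% versus 39%, two-sided alpha 0.05, power 85%, 378 per group analysed, 397 recruited. For context, the usual two-proportion formula gives 365 per group without and 383 with continuity correction, so the stated 378 is of the right order.

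Power = Φ{[|p1 − p2|√n − 1.96√(2p̄(1 − p̄))] / √(p1(1 − p1) + p2(1 − p2))}. With n = 378 and p̄ = 0.445 this is Φ{(2.139 − 1.378)/0.6985} = Φ(1.09) = 86.2%.

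- Crossover, outcome kept: if share x of the 50% arm takes on the other arm's risk, p1 = 0.50 − 0.11x.
- Withdrawal, outcome lost: if share x of both arms is lost, n = 378(1 − x).

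| Assumed x | Crossover | Withdrawal |
|---|---|---|
| 2% | 84.8% | 85.5% |
| 5% | 82.6% | 84.4% |
| 10% | 78.4% | 82.4% |

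The first route dilutes the effect and the second removes outcomes. Neither costs much power at a small share.

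For the second route, possible bias matters more than power. As an extreme, suppose share x of the 50% arm only is lost and every lost patient had an unfavourable outcome. The observed rate is then (0.50 − x)/(1 − x):

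- x = 2%: 0.48/0.98 = 49.0%, a shift of 1.0 point.
- x = 5%: 0.45/0.95 = 47.4%, a shift of 2.6 points.
- x = 10%: 0.40/0.90 = 44.4%, a shift of 5.6 points.

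The planned difference is 11 points. The extreme shows the direction and the ceiling for each assumed share. It does not predict what happens in this trial.

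**The case against.** Several counter-arguments have force.

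- **Both routes are permissive.** Crossover is allowed and withdrawal may be used, by different decision-makers. This is an unresolved overlap, not two mandatory rules in collision. That stands, but the overlap still lets the status vary by site.
- **Violation (b) can be read sensibly.** The word for inappropriate use, and the naming of crossover and violation as alternatives, suggest that permitted crossovers were meant to be excluded. That is a fair guess at the intention; the definition itself does not say so. With no per-protocol or as-treated set, the label cannot change the primary estimate.
- **Intention to treat may be meant to cover withdrawn patients.** Possibly, but follow-up after an investigator's withdrawal is nowhere stated.
- **The source is a condensed article.** Coding rules may sit in the full protocol. The two sections nevertheless differ as published.

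A reader might infer more than the documents support:

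- *That departures cannot be counted, or that a one-day bleed and a 25-day change of strategy look alike.* *Plans for assessment and collection of outcomes* records daily minimum and maximum Hb, each unit transfused in the ICU, and the reason and time of premature termination. Within the ICU, duration and direction can be reconstructed. After ICU discharge they may not be.
- *That departures fall almost only in the restrictive arm.* The crossover rule speaks of a higher Hb without a figure, Table 1 contemplates cardiac targets above 9 g/dL, and bleeding can lead to transfusion at or above 9 g/dL in either arm.
- *That every crossover reason meets (b).* Lack of blood involves no transfusion; it could only fall under (a).
- *That "Transfusion thresholds are maintained until a maximum of 28 days after randomization or hospital discharge/death, whichever occurs first" is a further contradiction.* It states the default duration, and the next section gives the exceptions.

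**Conclusion.** The concern holds in limited form. The two sections give the same coronary event different dispositions without saying how they relate, and the disposition can decide whether the 180-day eGOS is available. Violation (b), read literally, overlaps with permitted crossover and can inflate the violation count used for compliance reporting, without touching the primary estimate.

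The size is unknown. Event rates are not given and the split between arms cannot be derived. The 2% to 10% range is assumed, and the article itself expects very few crossovers. Table 1 also excludes patients with a cardiac need for Hb above 9 g/dL and those with uncontrolled bleeding at enrolment. Effects on power are small at low shares. The remaining risk is site-dependent loss of outcomes after a harm event. Priority: minor.

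**What to change.** 1. Reconcile *Interventions: modifications* with *Informed consent* so that the coronary event has one disposition, the same in both arms. Which one is for the clinical team; none is proposed here.
2. State that stopping the assigned threshold, including a stop by the investigator for safety, is not withdrawal from follow-up. The 180-day eGOS and serious adverse events are still collected and analysed as randomized unless consent is withdrawn.
3. Report four categories separately by arm: permitted crossover, protocol violation, investigator stop for safety, and consent withdrawal. Exclude recorded permitted crossovers from violation (b).
4. Recode existing entries, blind to outcome, from the recorded reasons, the unit-level transfusion data and daily Hb.

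The cost is a wording change, a recode and some site queries, mainly for periods after ICU discharge. With 791 of 794 patients recruited, new wording will affect few new inclusions. Data collection is planned to run to June 2023 (*Trial status*), so outcomes of patients who were stopped can still be sought where consent allows.

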## Objectives

Our primary research question is to determine whether a “liberal” strategy of maintaining Hb concentrations at 9 g/dL or higher would result in a different neurological outcome when compared to a “restrictive” approach to RBC transfusion maintaining Hb concentrations at 7 g/dL or higher in critically ill patients with anemia (Hb ≤ 9 g/dL) and acute brain injury. We expect fewer complications in the restrictive group but an improvement in brain oxygenation in the liberal group, with a potential impact on neurological outcomes.

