### Interim analysis

Initially, two interim analyses (i.e., after 200 and 700 patients) were scheduled; however, one interim analysis at 300 patients was therefore decided to assess for protocol compliance, main outcome, and SAEs, according to data collection completeness. An independent statistician, who has access to the whole database, reported these data to the DMSC by maintaining the blinding for the study groups (i.e., group A vs. group B). After the analysis of this report, the DMSC sent a report to continue the study recruitment without any safety issue.

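### The protocol-violation definition does not count a transfusion withheld below 7 g/dL in the restrictive arm, so violation counts are one-sided there and not comparable between arms

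*Protocol article*

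**What the plan says.** Under *Interventions: description* the restrictive rule is an instruction to act: "Patients randomized to the lower Hb threshold for transfusion receive packed RBC transfusion whenever their Hb concentration is < 7 g/dL". The liberal arm gets the same kind of instruction at 9 g/dL. The Abstract likewise describes "a “restrictive” approach in which the aim is to maintain Hb concentrations greater than 7 g/dL", and *Objectives* also gives that arm a floor at 7 g/dL.

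*Interventions: modifications* defines a protocol violation by a closed list of three limbs:

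- Limb (a), restrictive arm: "inability to maintain the daily max Hb values < 9 g/dL in the restrictive group and avoid transfusion until Hb drops below 7 g/dL".
- Limb (a), liberal arm: "OR > 9 g/dL in the liberal group for two consecutive days".
- Limb (b): "one or more transfusions given inappropriately (i.e., in contradiction of the assigned trigger level".
- Limb (c): "error in type/cross-match between donor and recipient".

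The same section lets the treating physician cross a patient to the other arm, for example when blood is lacking, and has the reason entered in the eCRF. *Interim analysis* reports that "one interim analysis at 300 patients was therefore decided to assess for protocol compliance, main outcome, and SAEs".

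**The concern.** Each arm's rule has two sides: transfuse below the trigger, and do not transfuse above it. A violation definition should detect a departure on either side. This one appears to police the floor in the liberal arm and only the ceiling in the restrictive arm.

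What is at stake is whether readers can tell if each strategy was delivered. The *Background* criticises an earlier trial because achieved Hb lay well above the assigned levels, and the *Discussion* concedes that separation here will not be very large. The protocol plans no per-protocol or as-treated analysis, so violation and crossover records are the main stated evidence on delivery. If some restrictive patients were kept below 7 g/dL without transfusion, that arm was managed more severely than described, and the violation table would not show it. Such omissions are conceivable: *Sample size* says the pandemic disrupted blood availability, and the *Discussion* says supply depends on local organization.

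**Working it through.** There is no stated figure to reproduce. The check applies the three limbs, as written, to constructed patients. The Hb values are illustrative and do not come from the protocol.

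**Rule as coded**

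- Limb (a), restrictive: daily maximum Hb at or above 9 g/dL, or a transfusion given with Hb at or above 7 g/dL.
- Limb (a), liberal: daily maximum Hb at or below 9 g/dL on two consecutive days.
- Limb (b): any unit given with Hb at or above the assigned trigger (7 or 9 g/dL).
- Limb (c): cross-match error; none in these cases.

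**Results**

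| Constructed patient | Departs from assigned trigger? | (a) | (b) | (c) | Violation? |
|---|---|---|---|---|---|
| Restrictive, Hb 6.2–6.6 for 5 days, no transfusion | Yes | No | No | No | **No** |
| Liberal, same values, no transfusion | Yes | Yes | No | No | Yes |
| Restrictive, transfused once at Hb 8.0 | Yes | Depends on reading | Yes | No | Yes |
| Liberal, one day at 6.2–6.6, then transfused and above 9 | Yes, for one day | No | No | No | No |

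The first three rows were run as a coded rule. The fourth follows by hand: limb (a) needs two consecutive days, and the unit was given below the trigger.

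**Does the wording allow another reading?**

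- It is unclear whether the two-day condition in limb (a) also governs the restrictive arm. That decides limb (a) in row three, but not row one, where neither reading is met: the maximum is below 9 g/dL and nothing was transfused.
- The word *until* in limb (a) says when the ban on transfusing ends. It does not create a duty to transfuse afterwards.
- The reference in limb (b) to the assigned trigger qualifies transfusions given, so it does not reach transfusions withheld.
- The crossover clause does not help. It concerns a move to the other arm. A restrictive patient left below 7 g/dL has not moved to the liberal strategy, and there is no lower arm to move to.

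**What the listed data can show** (*Plans for assessment and collection of outcomes*)

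- Daily minimum and maximum Hb and each transfused unit are recorded, but only during the ICU stay. Thresholds apply for up to 28 days, or until hospital discharge or death.
- Hb immediately before each unit is not listed. On a restrictive-arm day with minimum 6.8 and maximum 8.4, one cannot tell whether a unit was given below 7 g/dL. Units given on days when even the minimum was not below the trigger are certain departures, so their count is a lower bound.

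**The case against.** The best case against the point is that it concerns a label. Daily Hb and each unit are in the eCRF, so an ICU patient at 6.2 g/dL with no unit recorded is visible in the data. The analysis is intention-to-treat, violation status excludes nobody and enters no stated model, and the trial is pragmatic by design. Nothing in the document says that any restrictive patient went untransfused below 7 g/dL. Derivation rules and adherence tables usually belong in the full protocol or the analysis plan.

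Much of this stands, and it rules out three stronger readings that a reader might infer:

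- *Such a patient is certified as fully compliant.* The protocol has no such category; the patient simply meets no violation criterion.
- *The committee's review at 300 patients could not see under-transfusion.* The article does not say that compliance was judged only by these three limbs, and the independent statistician had the whole database. That review is also past.
- *The primary result is biased by the definition.* Any effect on outcome would come from the care delivered, whether or not it was flagged.

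What does not stand is the appeal to missing detail. The article prints a closed definition that disagrees with its own intervention rule and treats the two arms differently. That is a rule fixed badly, not one left for another document.

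**Conclusion.** The point holds as a mismatch between the violation definition and the intervention. Taken literally, none of the transfusions withheld below 7 g/dL in the restrictive arm can count as violations, whereas a shortfall lasting two consecutive days in the liberal arm does. A shortfall of a single day is missed in both arms. A difference in violation counts between arms therefore cannot be read as a difference in adherence.

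The number of patients affected is unknown: the document bounds it only between 0 and the 397 planned for the restrictive arm. The consequence is limited to compliance and separation reporting and to the interpretation of the strategy contrast; the intention-to-treat estimate is unchanged. The conclusion rests on reading the three limbs as the complete definition, which is how the section presents them. It is worth correcting before analysis because the correction is cheap.

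**What to change.** Reconcile *Interventions: description*, *Interventions: modifications* and *Objectives* so that a violation covers departures from the assigned trigger in both directions and in both arms. This changes no clinical threshold.

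Before analysis, derive from the eCRF and report by arm:

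1. ICU days with minimum Hb below the assigned trigger and no RBC unit recorded within a stated interval.
2. Units given on days when even the minimum Hb was not below the assigned trigger, labelled as a lower bound.

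The cost is a wording change and a derivation from data already collected. With 791 of 794 patients recruited according to *Trial status*, the benefit lies mainly in analysis and reporting rather than conduct. The downsides are that reported compliance may look somewhat less favourable, and that the measure covers the ICU stay only, not the full threshold period of up to 28 days; the report should say so.
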